### Sample size

2.4

No clinical trial has been conducted to evaluate the efficacy of GJS compared with placebo on the SCORAD index for AD. Therefore, we determined a required sample size of 23 per group based on recommendations by a previous statistical study.^[17]^ Considering an assumed dropout rate of 20%, 58 participants, 29 in each group will be required.

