#### Atopic dermatitis symptoms

2.8.1

Disease severity and quality of life will be assessed using SCORAD, the eczema area and severity index (EASI), the Dermatology Life Quality Index (DLQI), and EuroQoL 5 dimensions 5 levels (EQ-5D-5L), respectively. The primary outcome of the present study is the difference between the SCORAD of the 2 study groups before (week 0) and after (week 8) medication has been administered. SCORAD, EASI, DLQI, and EQ-5D-5L also will be assessed at week 0, 4, and 8.

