#### Safety outcomes

2.8.5

For the safety of the study participants, complete blood cell counts, liver function tests, lipid tests, and urine analyses will be performed at the screening phase and end of the trial. Vital signs will be examined at every visit. For female participants, urine human chorionic gonadotropin (hCG) will be checked at the screening visit to test for pregnancy. The investigator will ask about any expected or unexpected adverse events and record details of adverse events in the case report form (CRF). When serious adverse events occur, the investigator will immediately report this to the institutional review board (IRB) within 24 hours. If a serious adverse event occurs, the investigators will determine whether it is acceptable, whether the experimental drug should be continued or stopped, and whether the trial should be amended or ended.

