### Statistical analysis

2.10

The measured variables, including the primary and secondary outcomes, will be assessed using the full analysis set based on the intention-to-treat principles. The per-protocol analysis set will be used for the sensitivity analysis. The baseline characteristic values in both groups will be expressed as a mean and standard deviation for continuous variables that are normally distributed or medians and interquartile ranges for non-normal data. Frequencies and percentages will be used to present categorical variables. Baseline differences between groups will be assessed using an independent 2-sample *t* test or Wilcoxon rank-sum test for continuous variables. The Chi-square test or Fisher exact test will be used for categorical variables. A mixed-effect model repeated measure (MMRM), which sets participants as a random factor and the group and visit as fixed factors, will be performed to analyze the between-group differences in the primary and secondary outcome measures. The Student paired *t* test and repeated-measures analysis of variance (ANOVA) will be used to evaluate the intra-group time changes in continuous values. Chi-square or Fisher exact tests will be used to evaluate the intra-group time changes in categorical values. MMRM does not require the replacement of missing data, and the missing data in the intra-group analysis will be replaced using the last observation carried forward method. The level of significance will be set at 0.05 (2-tailed). All analyses will be performed by an independent statistician using SAS version 9.4 (SAS Institute Inc., Cary, NC).

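### Within-group changes in categorical measures are assigned to chi-square or Fisher exact tests, which ignore that the same participants are measured at each visit (minor correction)

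*Protocol article*

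**What the plan says.** Section 2.10 of the Protocol article sets separate rules for within-group change by type of variable.

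- Continuous measures: "The Student paired *t* test and repeated-measures analysis of variance (ANOVA) will be used to evaluate the intra-group time changes in continuous values".
- Categorical measures: "Chi-square or Fisher exact tests will be used to evaluate the intra-group time changes in categorical values".

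Earlier in the section the same two tests are named for comparing the groups at baseline: "The Chi-square test or Fisher exact test will be used for categorical variables". The two arms are independent samples there, so that use is sound.

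The measurements are repeated on the same people. Section 2.8.1 says "SCORAD, EASI, DLQI, and EQ-5D-5L also will be assessed at week 0, 4, and 8". Section 2.8.5 says "complete blood cell counts, liver function tests, lipid tests, and urine analyses will be performed at the screening phase and end of the trial". The significance level is 0.05, two-sided. No paired method for categorical data is named anywhere in the article.

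**The concern.** A change over time within one arm is a paired comparison. A chi-square or Fisher test can be applied to such data in two ways, and neither answers the question.

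1. **Visit-by-category counts.** Each participant enters the table two or three times as if they were different people. The standard error ignores the within-person correlation.
2. **Baseline-by-week-8 cross-table.** Each participant enters once, but the null hypothesis is that the week 8 category is unrelated to the baseline category. A stable measure rejects that hypothesis strongly although nothing has changed.

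This is a stated method and not a detail left to an analysis plan. It also departs from the pairing that the section respects for continuous data. A statistician who followed the sentence literally would report p-values that do not have their nominal meaning.

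**Working it through.** **The plan's own figure.** Section 2.4 gives "we determined a required sample size of 23 per group based on recommendations by a previous statistical study" and then "Considering an assumed dropout rate of 20%, 58 participants, 29 in each group will be required". Check: 23 / (1 − 0.20) = 28.75, rounded up to 29 per group, and 2 × 29 = 58. This reproduces and is not in dispute. It supplies n = 29 per group below.

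**Assumed inputs.** The article gives no category proportions and no within-person correlation r. Both are assumptions here, shown over a range.

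**Reading 1, type I error.** Suppose the true proportion p is the same at both visits.

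- Variance used by the unpaired test: 2p(1 − p)/n.
- True variance of the paired difference: 2p(1 − p)(1 − r)/n.
- The unpaired test therefore rejects only when the correctly scaled statistic exceeds 1.96/√(1 − r), so the true error rate is 2 × [1 − Φ(1.96/√(1 − r))].

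| r | 1.96/√(1 − r) | True error rate |
|---|---|---|
| 0 | 1.960 | 5.0% |
| 0.3 | 2.343 | 1.9% |
| 0.5 | 2.772 | 0.6% |
| 0.7 | 3.578 | 0.03% |

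A simulation (20,000 replicates, n = 29, 50% at both visits) agrees for chi-square: 0.049, 0.017, 0.006 and 0.0003. Fisher is lower still: 0.024, 0.007, 0.002 and 0.0001. At r = −0.3 the chi-square rate rises to 0.084.

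**Reading 2, cross-table.** Take 29 participants, 15 positive at both visits and 14 negative at both, so that nobody changes. The chi-square statistic is 29 × (15 × 14)² / (15 × 14 × 15 × 14) = 29, far above the 3.84 cut-off. More generally, with 50% at both visits and no change, the simulated rejection rate for chi-square is 39%, 81% and 99% at r = 0.3, 0.5 and 0.7. For Fisher it is about 27%, 71% and 98%.

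**Power under reading 1.** Assume n = 29 and a fall from 70% to 45%. If a share w of all participants worsens, then a share w + 0.25 improves. Exact multinomial enumeration gives:

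| Worsen (w) | Improve | Implied r | Exact McNemar | Chi-square | Fisher |
|---|---|---|---|---|---|
| 0.9% | 25.9% | 0.55 | 72% | 46% | 31% |
| 3% | 28% | 0.46 | 62% | 47% | 33% |
| 10% | 35% | 0.15 | 43% | 48% | 36% |

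Simulation gives the same McNemar and chi-square pairs to within about one percentage point (72/45, 62/46, 44/49). The first row, at 0.9%, has almost nobody worsening. In the last row exact McNemar falls below chi-square, because the correlation is low and the exact test is itself conservative.

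**The case against.** Most of the case on the other side concerns size, and most of it stands.

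- **The main analyses do not use this rule.** Section 2.10 assigns between-group differences in the primary and secondary outcomes to a mixed model. Within-group change does not estimate a treatment effect in a placebo-controlled trial. A reader might infer that the trial's main conclusion is at risk; the article does not support that.
- **No affected endpoint is named.** SCORAD, EASI, DLQI, KGSRS and NDI-K are scales, and the IgE and ECP results are measured levels. A reader might point to EQ-5D-5L dimension levels, specific-IgE positivity or abnormal laboratory values. These are plausible uses, but the article describes no categorical analysis of any of them.
- **The error is not uniform.** Under reading 1 it vanishes at zero correlation, and with positive correlation it makes the test too cautious. A reader might infer false claims of benefit, or that a paired test always gains power. The first would need the cross-table reading, which nothing in the section shows to be intended, or a negative correlation. The second fails in the last row of the power table.

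The wording could also be defended as shorthand, since McNemar's statistic is referred to a chi-square distribution. That does not hold up: naming Fisher as the alternative, and naming the same pair for baseline comparisons, points to the ordinary independent-sample tests.

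None of this makes the stated tests suitable for paired data.

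**Conclusion.** The point holds as a minor correction of a method that is stated wrongly. The type I figures follow from a standard formula and depend only on the assumed correlation. The power differences depend on assumed proportions and worsening rates; they run from a gain of about 26 percentage points to a loss of about 5 for exact McNemar against chi-square, so no single figure should be quoted. The effect is confined to within-group p-values for whatever categorical measures are analysed. The primary SCORAD comparison, the between-group results and the sample size of 58 stand as they are.

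**What to change.** Replace the sentence on categorical within-group change with a paired rule:

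- binary measures at two visits: McNemar's test, in its exact form when discordant pairs are few;
- more than two categories at two visits: Bowker's or the Stuart-Maxwell test;
- binary measures at three visits: Cochran's Q, or GEE with participant as the cluster.

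State that chi-square and Fisher exact tests are kept for between-group comparisons only. It would also help to name the categorical measures to which the rule applies.

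The cost is one sentence of analysis wording and standard procedures in SAS. Data collection, trial conduct and sample size do not change.

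### Within-arm change is tested on LOCF-filled data beside an MMRM without imputation, so reported arm-level changes can be biased and their p-values cannot isolate a drug effect

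*Protocol article*

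**What the plan says.** All the analysis rules are in section 2.10 (Statistical analysis) of the protocol article.

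- **Between groups.** An MMRM with participant as random factor and group and visit as fixed factors "will be performed to analyze the between-group differences in the primary and secondary outcome measures". On missing values, the article notes that "MMRM does not require the replacement of missing data".
- **Within groups.** The paired t test and "repeated-measures analysis of variance (ANOVA) will be used to evaluate the intra-group time changes in continuous values". For these tests, "the missing data in the intra-group analysis will be replaced using the last observation carried forward method".
- **Level.** One two-sided 0.05 level is given for the whole section. The within-group tests are not set apart from it.

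Three other sections bear on the point. Section 2.4 (Sample size) expects losses: "Considering an assumed dropout rate of 20%, 58 participants, 29 in each group will be required". Section 2.8 (Outcome measurement) puts the clinical scores at weeks 0, 4 and 8, but total IgE, ECP and the fecal samples at weeks 0 and 8 only. Section 2.3.1 (Inclusion criteria) admits participants on a SCORAD band of 25 to 50, and SCORAD is the primary scale.

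**The concern.** There are two separate problems.

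**Two missing-data rules for one outcome.** The MMRM uses the observed visits and is valid if data are missing at random. LOCF assumes that a participant's score stays where it was last seen, and then counts the filled value as an observation. Anyone lost before week 4 enters with a change of exactly zero. For IgE and ECP, LOCF can carry only baseline, so every dropout enters as zero change. The two arm-level changes in the report then need not subtract to the MMRM contrast printed beside them.

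**Before-after p-values.** A test inside one arm cannot separate a drug effect from placebo response, natural course or regression to the mean. The last is a real possibility when entry depends on a band of the outcome scale itself, in a disease that the Introduction describes as relapsing. If one arm reaches 0.05 and the other does not, a reader may take the split as evidence of efficacy.

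At stake is how the arm-level results are reported and read. The primary test is not at stake.

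**Working it through.** **1. The plan's own figure.** Section 2.4 states: "we determined a required sample size of 23 per group based on recommendations by a previous statistical study". With 20% dropout, 23 / 0.8 = 28.75, rounded up to 29 per arm, or 58 in total. This agrees with the article. The 23 cannot be derived, because no effect size, SD or power is given.

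**2. LOCF and the mean change.** The article gives no trajectory, so one is assumed: a true arm change of -6 at week 4 and -10 at week 8, with dropouts who would have changed as the others did. With dropout d and a share q of dropouts leaving before week 4:

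LOCF mean change = (1 - d)(-10) + d[q × 0 + (1 - q)(-6)]

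| Dropout d | all leave after week 4 (q = 0) | half and half (q = 0.5) | all leave before week 4 (q = 1) |
|---|---|---|---|
| 10% | -9.6 (4% shrinkage) | -9.3 (7%) | -9.0 (10%) |
| 20% | -9.2 (8%) | -8.6 (14%) | -8.0 (20%) |
| 30% | -8.8 (12%) | -7.9 (21%) | -7.0 (30%) |

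If the full analysis set requires a post-baseline value, those lost before week 4 drop out of the calculation. At d = 20% the shrinkage is then 8% for q = 0, 4.4% for q = 0.5 (8.6 / 0.9 = 9.56 against 10) and 0% for q = 1.

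Unequal dropout shows how arm-level changes can depart from the contrast. Suppose both arms truly change by -10, with 10% lost in one arm and 30% in the other, half of each before week 4. LOCF reports -9.3 and -7.9, an apparent difference of 1.4 where there is none.

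**3. LOCF against a likelihood-based estimate.** One large simulated arm (200,000 participants) had assumed means of 38, 32 and 28, variances of 50, 100 and 100, and covariances of 35 (weeks 0 and 4), 30 (weeks 0 and 8) and 60 (weeks 4 and 8). Dropout came after week 4, depended on the week-4 score, and reached 19.4%. The true change was -10.0, the likelihood-based estimate -10.0, completers only -10.4, and LOCF -8.8.

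**4. IgE and ECP.** With no week-4 measurement, the LOCF mean is (1 - d) times the true change. At 20% dropout that is 20% shrinkage, if dropouts would have changed as completers did and are kept in the analysis.

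**5. LOCF and the within-arm test.** Counting 29 instead of 23 as observed multiplies the standard error by sqrt(23/29) = 0.89 if the spread is unchanged. Relative to completers only, the t statistic is multiplied by 0.80/0.89 = 0.90, 0.86/0.89 = 0.97 or 0.92/0.89 = 1.03 across the 20% row. The two effects largely cancel, so the problem lies in the estimate more than in the test.

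**6. Split significance with no drug effect.** Let both arms share a standardised change (mean change divided by SD of change), again assumed. Let p be the noncentral-t probability that one arm is significant at two-sided 0.05, and u the part of p in the direction of improvement. The chance that GJS improves significantly and placebo is not significant is u(1 - p).

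| Standardised change | n = 29: p | n = 29: GJS only | n = 23: p | n = 23: GJS only |
|---|---|---|---|---|
| 0.2 | 18% | 15% | 15% | 13% |
| 0.3 | 35% | 23% | 28% | 20% |
| 0.5 | 74% | 19% | 63% | 23% |
| 0.8 | 99% | 1% | 96% | 4% |

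A between-group test would err in that direction 2.5% of the time. These figures assume complete data and do not depend on LOCF.

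**The case against.** The strongest reply is that nothing here reaches the primary inference. That is right. Section 2.8.1 defines the primary outcome as a difference between the groups, section 2.10 gives that comparison to the MMRM, and LOCF is confined to the within-group analysis. A reader might infer that the trial's main result is compromised, or that the sponsor plans to claim efficacy from within-group p-values. The article says neither. A descriptive label may also stand in an analysis plan that is not shown, so its absence is not the finding. The finding is that the article fixes LOCF and fixes these tests.

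A second reply is that the bias is conditional. That also stands. It vanishes if no visits are missed or if nothing changes after the last visit, and its size depends on timing and trajectory, which the article does not give. The 20% is a planning allowance, and some withdrawals under section 2.3.3 may still have week-8 data. So the arm-level changes can differ from the MMRM; it cannot be said that they will.

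A third reply is that LOCF hardly moves the within-arm test, because the smaller mean and the smaller standard error offset each other. Step 5 bears this out. The reading that LOCF manufactures within-arm significance is not supported.

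Finally, split significance is rare when the common change is large (1% at 0.8 with 29 per arm), and counting splits in either direction would double the figures for GJS alone. The table therefore gives one direction over a range.

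What remains is that the plan, followed as written, analyses the same outcomes under two incompatible assumptions and tests a quantity that cannot isolate the drug's effect.

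**Conclusion.** The point holds as a secondary matter of estimation and reporting. At the planned 20% dropout and the assumed trajectory, LOCF shrinks the arm-level change in clinical scores by about 8% to 20%, or by 0% to 8% if a post-baseline value is required. For IgE and ECP each dropout retained in the analysis counts as no change. A likelihood-based estimate does not share this bias when data are missing at random.

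Independently of LOCF, within-arm p-values can favour GJS alone in roughly one trial in five with no drug effect, if the common standardised change is 0.3 to 0.5. The chance is 15% at 0.2 and 1% at 0.8, all at 29 per arm. The trajectories, dropout timing and standardised changes are assumptions. Only the 20%, the 23 and 29 per arm, the visit weeks and the 0.05 level come from the article.

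**What to change.** In section 2.10:

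1. Delete LOCF.
2. Add a group-by-visit term to the MMRM. The article lists only group and visit as fixed factors. If baseline is one of the responses, that model forces both arms to change in parallel. If the response is change from baseline, it forces the same group difference at weeks 4 and 8. Neither gives free arm-by-visit estimates.
3. Report arm-level changes with 95% confidence intervals from that model at each post-baseline visit where the outcome is measured, which means weeks 4 and 8 for the clinical scores.
4. For outcomes measured only at weeks 0 and 8, report the week-8 change without LOCF, with the number of participants measured.
5. State that all within-arm results are descriptive and that efficacy rests only on the between-group contrast.

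The cost is minor rewording and the loss of the within-group p-values as formal tests. No further data or participants are needed, and fewer analyses are run.

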### Ethics and dissemination

2.11

This study was approved by the IRB of Kyung Hee University Korean Medicine Hospital at Gangdong (KHNMCOH2019-06-002-001, version 1.4, 11-SEP-2019). This trial has been registered at the Korean National Clinical Trial Registry, Clinical Research Information Service (KCT0004299) before the recruitment, which is a primary registry of the World Health Organization International Clinical Trials Registry Platform. This study was also approved by the MFDS for the investigational new drug (IND) tract. Any protocol modifications will be approved by the IRB of the Kyung Hee University Korean Medicine Hospital at Gangdong and MFDS.

The trial will be performed in compliance with the Declaration of Helsinki, and according to Good Clinical Practices as described by the MFDS. Written informed consent will be obtained by the investigator from all participants prior to enrollment. The written informed consent form will include information on the background and purpose of the study, experimental and placebo drugs, outcome measures, and possible benefits and harms. The participants will be immediately notified when new facts regarding the study are found. The investigator will explain the study in non-scientific language. All participants will be given enough time to decide whether they wish to participate in the trial. The confidentiality of their personal information will be protected. Throughout and subsequent to the trial, all documents and data will remain secure in a locked cabinet or as password-protected computer files.

Investigator, sponsor, CRA, and IRB members associated with this study can access the records of the participants for the purpose of managing the monitoring, testing, and progress of this study. And auditor from the MFDS can access the records in order to audit whether the trial was conducted in accordance with law and regulation. All documents, including the CRF, must be recorded by the participant's identification code (generally the participant's initials) and not the participants’ name.

## Discussion

3

AD is a long-standing inflammatory skin disease. Therefore, it is necessary to develop medicines that have no adverse effects when used for long-term therapy. Conventional treatment for AD has been focused on directly reducing the inflammation. However, there have been many limitations of such treatment with adverse effects after long-term use, symptoms relapse after the discontinuation of medication, and refractory cases for medications.

Extensive research has investigated the interaction of the gut microbiota with nutrition, metabolism, physiology, and immune function. Many reports have identified a link between microbiome and many chronic conditions such as obesity, inflammatory bowel diseases, diabetes mellitus, allergic rhinitis, and AD.^[18–22]^ Selective modulation of host-microbiome using pro-, pre-, synbiotics to treat AD has been of particular interest to many investigators.^[23]^

For many decades, many herbal drugs have demonstrated their efficacy and safety in treating AD. A Cochrane systematic review of 28 studies involving 2306 participants found that an orally administered herbal drug could improve the quality of life in children with AD.^[24]^ However, further well-designed clinical studies are needed to determine the efficacy of herbal drugs.

An increasing number of studies have demonstrated that the therapeutic effect mechanism of herbal drugs is linked with gut microbiota.^[25]^ Many clinical studies that have reported the efficacy of herbal formulas in treating AD have observed skin symptoms using SCORAD and EASI and assessed the modulation of immune biomarkers such as serum IgE, eosinophil counts.^[24]^ To date, no clinical studies have evaluated the efficacy of herbal drugs on gut microbiota in patients with AD. In the present study, GJS will be administered for 8 weeks. Its impact on skin symptoms, systemic immune biomarkers, and gut microbiota will be evaluated.

To our knowledge, this is the first clinical study to investigate the efficacy of GJS for patients with AD, as well as the first study to investigate the efficacy of herbal drugs on gut microbiome. This study will provide evidence regarding the use of GJS in treating AD.
